### Sample size

According to previous multicenter controlled studies [3, 14], sample size calculation was performed considering that under the assumption of normal distribution of the scores (primary outcomes differences between groups) and considering α level of .05, a sample size of 30 subjects resulted in a power greater than 70% and was therefore considered as adequate for this trial. To avoid loss to follow-up and maximize the follow-up sample, standard procedures (regular phone contacts with participants) will be applied.

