### Statistical analyses

Statistical analyses on outcome measures will be conducted using SPSS. We will look at statistically significant changes in primary and secondary outcome measures from T_0 (start of treatment) to T_1 (end of treatment), i.e. a training effect. Moreover, we will look for a treatment (Ability vs. TAU) effect and at training x treatment interactions. This will be done through a 2-way ANOVA. Post hoc analysis will be applied to compare Ability with TAU. An alpha ≤ 0.05 will be considered significant. Moreover, score modification at T_2 (after 12 months) in both groups will be evaluated by means of regression analyses over time considering previous values at baseline and T_1. Contributing factors that may predict changing in outcomes will be also examined in a multivariate interval regression analysis. Moreover, each outcome will be categorized in three intervals according to the criterion of a clinical improvement/stability/impairment which was set by expert physicians. Given the exploratory nature of the study, a stepwise forward model will be set with an entrance alpha level of 0.10. Model assumptions and goodness of fit were evaluated by means of the proportionality of odds across response categories test and the association between predicted and observed values (Spearman rho). When the proportionality of odds assumption is violated, a generalized logistic regression model will be computed. For each significant model, several representative profiles and their associated probability of a successful treatment will be computed.

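### Stepwise selection at entry level 0.10 in 30 people, with success probabilities taken only from significant models, will give selection-biased profiles; how often they rest on noise depends on an unstated number of candidates

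*Protocol article*

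**What the plan says.** All of this is in the Statistical analyses section of the protocol article, after the 2-way ANOVA of change from T0 to T1 and the regression for T2.

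- Predictors of change are "also examined in a multivariate interval regression analysis".
- In addition, "each outcome will be categorized in three intervals according to the criterion of a clinical improvement/stability/impairment"; the criterion comes from expert physicians.
- Predictors are chosen by forward entry, and the reason is given in the same sentence: "Given the exploratory nature of the study, a stepwise forward model will be set with an entrance alpha level of 0.10".
- Model assumptions and fit are judged "by means of the proportionality of odds across response categories test" and by the Spearman correlation of predicted with observed values. If proportional odds fails, a generalized logistic model replaces the first model.
- The output is stated as: "For each significant model, several representative profiles and their associated probability of a successful treatment will be computed".

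The total sample is 30, allocated 1:1. The article does not list the candidate predictors. It describes no shrinkage, internal validation or multiplicity control for this step.

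**The concern.** Forward selection picks the predictor that looks best in the sample and then fits and tests it on the same people. The coefficients, p-values and predicted probabilities ignore that search. A second filter follows, because profiles come only from models that reached significance, and those are the ones in which chance pushed the fit furthest. With 30 people and an entry level of 0.10, both filters act strongly.

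The named checks would not reveal this. The proportional-odds test concerns the shape of the model, not overfitting. The Spearman correlation is computed in sample, and overfitting improves it.

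Two further features make matters worse. Cutting scores into three classes discards information. A generalized logit for three classes also has 3 − 1 = 2 slopes per predictor where the cumulative logit has one, on the same 30 people.

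The model is also not clearly named: interval regression and a proportional-odds check belong to different models.

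At stake is the credibility of the probabilities of treatment success, which are easily read as describing which patients benefit.

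**Working it through.** **The plan's own figure.** The only computed figure is in the Sample size section: "a sample size of 30 subjects resulted in a power greater than 70" percent. It states no effect size or SD, so it cannot be reproduced, and it does not concern the stepwise models. No error rate is stated for those models.

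**Inputs from the article.** N = 30; entry level 0.10; three outcome classes; significance at 0.05. That last level is stated for the analyses in general. I assume that a significant model means overall p < 0.05.

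**Assumptions, not in the article.** k = 5 to 15 independent candidate predictors, none truly related to outcome.

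**Step 1. Chance that at least one noise predictor enters.** P = 1 − (1 − 0.10)^k.

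- k = 5: 1 − 0.9^5 = 0.41
- k = 7: 1 − 0.9^7 = 0.52
- k = 10: 1 − 0.9^10 = 0.65
- k = 15: 1 − 0.9^15 = 0.79

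An entry level of 0.05 would give 0.23, 0.40 and 0.54 for k = 5, 10 and 15, so tightening the level does not solve the problem.

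**Step 2. Simulated forward selection, n = 30, pure noise.** The ordinal runs used a proportional-odds model with three equal classes and likelihood-ratio entry at 0.10 (200 to 300 runs per setting, simulation error about 3 percentage points).

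| k | Any entry | Final model p < 0.05 | Median 10th to 90th percentile of fitted success probability, significant models (truth 0.33) |
|---|---|---|---|
| 5 | 44% | 28% | 0.14 to 0.62 |
| 10 | 71% | 57% | 0.09 to 0.62 |
| 15 | 88% | 77% | 0.05 to 0.69 |

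With a 25/50/25 split and k = 10, the figures are 68%, 53% and 0.06 to 0.49, where the truth is 0.25.

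A linear model on the continuous score is somewhat milder. The final model has p < 0.05 in about 25% of runs at k = 5, 46–48% at k = 10 and 66% at k = 15.

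**Step 3. Entry is not significance.** At k = 10 the ordinal rates are 71% for entry and 57% for an overall p below 0.05. In the linear model they are about 65% and 46–48%. Only the second rate bears on which models yield profiles.

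**Step 4. One real predictor among k (ordinal, 250 runs per setting).** Share of selected variables that are noise, for k = 5, 10 and 15:

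- moderate effect (log-odds 0.5 per SD): 55%, 75%, 85%
- strong effect (log-odds 1.0 per SD): 41%, 61%, 73%

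**Step 5. Scale, as illustration.** The assessment section lists about 9 participant scores. With k = 10 and nothing predictive, 9 × 0.65 = 5.9 models would be expected to contain a noise predictor. About 9 × 0.46 = 4.1 (linear) to 9 × 0.57 = 5.1 (ordinal) would appear significant.

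**The case against.** The strongest defence is that the step is labelled exploratory and is secondary. The treatment effect is estimated by a separate 2-way ANOVA, which this step cannot alter. The three classes follow a clinical criterion rather than an arbitrary cut. A condensed article may also leave the candidate list to the full plan, so its absence is no error. All of this stands, and it limits the point. It does not cure it: an exploratory label excuses a lenient threshold for generating hypotheses, but it does not make probabilities from significance-selected models unbiased.

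A reader might infer more than the article supports:

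- That the models will mostly report noise. This depends on the number of candidates and on true predictor strength, and the article gives neither. With 5 candidates it fails under the null (41–44% entry) and with one strong predictor (41% noise).
- That 6 to 9 of 13 outcome scores would yield spurious significant models. That multiplies 13 by the entry rate, not by the rate of significant models. It also adds four caregiver scales that the primary and secondary outcome list does not name.
- That randomised arm is left out. The text does not say whether arm is forced in, a candidate or excluded.
- That profiles will decide who is offered the programme. No section says so.
- That the proportional-odds test is unreliable at this size. This is plausible, but nothing in the article or in the calculations above establishes it.

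**Conclusion.** The point holds in conditional form. Followed as written, the plan produces success probabilities that are selected on significance, uncorrected, and checked only in the data that produced them.

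If nothing predicts outcome and there are 5 to 15 independent candidates, a noise predictor enters in about 40–80% of outcomes, and in over half from about 7 candidates. The final model appears significant in about 25–66% (linear) or 28–77% (ordinal). In such models with 10 candidates, fitted success probabilities run from about 0.09 to 0.62 when the truth is 0.33 for everyone.

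The sizes rest on the assumed candidate count, independent predictors, a global null and the reading of a significant model as overall p < 0.05. The direction of the bias does not depend on the exact count. The mismatch between interval regression and proportional odds is a matter of wording to reconcile. The randomised comparison is not in question.

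**What to change.** 1. Replace forward selection with one small pre-specified model per outcome on the continuous score. Always include arm and baseline score, plus at most one or two named factors (for example diagnosis, and age or education).
2. Report every such model with 95% CIs, significant or not, and label the results hypothesis-generating.
3. Show the improvement, stability and impairment classes as counts by arm.
4. Do not report profiles from significance-selected models. If profiles are kept, give them for all outcomes, with penalisation or a bootstrap optimism correction that repeats the selection step in each resample.
5. If a categorical model is retained, name one model type and make the assumption checks match it.

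The cost is small. Items 1 to 3 mean less analysis; keeping profiles under item 4 adds some programming. The real loss is that there would be no predictive profiles, or less striking ones.

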### Participants

Thirty participants will be consecutively recruited from the Memory Clinic of IRCCS Don Carlo Gnocchi Foundation.

Outpatients inclusion criteria will be the following: a) diagnosis of mild AD or MCI due to AD, according to DSM- 5 diagnostic criteria and AD/MCI diagnostic criteria [23, 1]; b) MMSE score >18 (Mini Mental State Examination, [15, 22]); c) aged over 65 years and d) with school attendance ≥3 years.

Exclusion criteria will be a) severe auditory and/or visual loss; b) overt severe behavioral disturbances. and c) recent (1 month or less before starting the program) introduction or dose modification of the following pharmacological treatments: cholinesterase inhibitor, memantine, antidepressant, or antipsychotic drugs. Low-dose benzodiazepines for insomnia will be allowed during the study.

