### Randomization and masking

Randomization will occur after screening and baseline assessments. Subjects will be randomly assigned to the Ability group or to the ACG with a 1:1 allocation ratio. Randomization will be conducted by an independent operator neither ot involved in the assessment and/or treatment using a computer algorithm (http://www.graphpad.com/quickcalcs/randMenu/). Since participants cannot be blinded to their treatment allocation, they will be instructed not to discuss the nature of their intervention with the researchers in charge of the assessments. Outcome measures will be collected by researchers blinded to group allocation.

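### After stepwise selection in 30 patients, same-data Spearman rho and profiles from significant models only tend to overstate the exploratory prediction models

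*Protocol article*

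**What the plan says.** All the steps are in the Statistical analyses section of the protocol article.

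- **Outcome:** "each outcome will be categorized in three intervals according to the criterion of a clinical improvement/stability/impairment".
- **Selection:** "a stepwise forward model will be set with an entrance alpha level of 0.10". The article justifies this by the exploratory nature of the study.
- **Fit:** a test of proportional odds, together with "the association between predicted and observed values (Spearman rho"). No threshold for rho is given.
- **Output:** "For each significant model, several representative profiles and their associated probability" of treatment success are to be computed.
- **Significance:** "An alpha ≤ 0.05 will be considered significant" is the general rule. The article does not say whether it also defines a significant prediction model.

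The Participants section fixes the sample: "Thirty participants will be consecutively recruited from the Memory Clinic". No second sample is mentioned. The number of candidate predictors is not given.

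**The concern.** A correlation between predictions and the observations that produced them measures fit plus over-fit. When predictors have been chosen by their association with those same observations, and there are only 30 of them, over-fit can account for most of the value. The proportional-odds test checks a model assumption and does not detect over-fitting.

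The significance filter adds to the problem. Models reach significance partly because chance made their coefficients large. Probabilities computed from unshrunken coefficients of only those models are therefore pushed away from the true values.

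What is at stake is how the output is read. A patient profile with a probability of successful treatment looks like clinical guidance. A reader who sees it beside a moderate, nominally significant rho has no means of telling how much of either is noise.

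**Working it through.** **The plan's own figure.** The article gives no figure for the prediction models. Its one design figure is a power above 70% for 30 subjects at alpha 0.05, with no effect size or SD, so it cannot be reproduced. With 15 per arm, the normal approximation Φ(d·√(15/2) − 1.96) reaches 70% at a standardised difference d of about 0.91 (two-sided). This does not bear on the present point.

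**Inputs from the article.** 30 patients, three ordered categories, forward entry at 0.10, profiles for significant models only.

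**Inputs assumed.** 5, 10 or 15 candidate predictors; the share of patients in each category; no true predictor unless stated otherwise.

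**Step 1: how often noise enters.** For p independent noise candidates, P(at least one enters) = 1 − 0.90^p. This gives 41% for p = 5, 65% for p = 10 and 79% for p = 15.

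**Step 2: why rho is sizeable once something enters.** Take one predictor and the usual t approximation, |r| = t/√(n − 2 + t²). Entry at 0.10 with n = 30 needs t of about 1.701, so |r| is at least 1.701/√(28 + 2.89) = 0.31. At 0.05, t is 2.048 and |r| is at least 2.048/√(28 + 4.19) = 0.36. With n = 300, entry at 0.10 needs only 1.650/√(298 + 2.72) = 0.10. The entry rule and the sample size alone thus put a floor under the apparent correlation.

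**Step 3: simulation with no true predictor, n = 30.**

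| Simulation | Models counted | Candidates | Median apparent rho | Rho in new patients |
|---|---|---|---|---|
| A: 25% improve, 300 runs per setting | any predictor selected | 5 / 10 / 15 | 0.39 / 0.46 / 0.54 | mean 0.00 each |
| B: one third per category, 600 runs per setting | overall p ≤ 0.05, at most 4 terms | 5 / 10 / 15 | 0.43 / 0.51 / 0.56 | median 0.00 each |
| C: separate repeat with noise candidates | any predictor selected | 5 / 10 / 15 | 0.36 / 0.42 / 0.50 | about 0 |

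In B, 30%, 55% and 72% of noise trials end in a significant model for a given outcome. In those models rho is itself significant at 0.05 in 87%, 92% and 95%.

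**Step 4: profile probabilities, no true predictor.**
- A, 10 candidates: patients at the 90th and 10th percentiles of predicted improvement are given 51% and 7%. The true value is 25% for all.
- B, profiles at ±1 SD on every selected predictor: medians of 57% and 12% (5 candidates), 72% and 6% (10), 82% and 3% (15). The true value is 33% for all.

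**Step 5: sensitivity in B, 10 candidates.**
- Only one term allowed: apparent rho 0.41, profiles 51% and 15%.
- 24 patients analysed (assumed loss by 12 months): rho 0.58, profiles 78% and 3%.
- One real predictor (log-odds 0.8 per SD): apparent rho 0.56 against 0.28 in new patients; favourable profile 77% against a true value of about 49%.
- n = 300, no true predictor: apparent rho 0.16. The small sample drives the size of the problem.

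**Step 6: how far bootstrap correction goes.** In B, selection was repeated in 25 resamples for each of 53 significant noise models with 10 candidates. Median rho fell from 0.48 to 0.20, so the correction removed (0.48 − 0.20)/0.48 = 58% of a value that should be zero. In C, about 0.13 to 0.21 remained, with a calibration slope of about 0.55 to 0.65.

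**The case against.** The strongest case on the other side has five parts.

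- **Rho is not a gate.** A reader might infer that models must pass the rho check before profiles are shown. The article does not say this. It sets no threshold for rho, and the only stated filter is significance. This stands.
- **A fit statistic describes fit.** The article claims neither validation nor accuracy in new patients, and it calls the study exploratory. A reader might infer that a validated tool is promised, but none is. This stands as to intent. The label does not make a same-data rho informative, and a probability of success for a patient profile goes beyond describing fit.
- **Internal validation may be in a full analysis plan.** That is possible, and its absence from an article would be no finding. The point here is what the article does fix: the rho measure and the significance filter. A plan that followed the text would carry both forward. Use of the same patients is an inference, though no other sample is named.
- **The inflation is not certain.** A reader might infer that noise models will always look accurate. In B, 28% to 70% of noise trials yield no significant model for a given outcome, and a rho of 0.4 to 0.55 is moderate. An all-null setting is the worst case: with one real predictor, some predictive value remains. This stands.
- **The root cause is the entry rule.** Inflated rho and extreme profiles do follow from selection at 0.10 in 30 patients. But the fit measure and the reporting filter are separate choices, and each can be changed separately.

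**Conclusion.** The point holds in a limited form. Once a model has been selected, apparent rho and profile probabilities tend to overstate performance. With no true predictor, rho is about 0.4 to 0.55 against about 0 in new patients. Profiles can differ by more than 40 percentage points where there is no real difference (51% against 7%, with 25% true for all). With one real predictor the overstatement is smaller but still clear.

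The direction held in every setting tried. The size rests on assumptions that the article neither confirms nor rules out: 5 to 15 candidates, the category shares, and fitting and checking in the same 30 or fewer patients.

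A reader might take this as a threat to the trial's main result. It is not one: the randomised Ability versus TAU comparison by ANOVA does not use these models. The change is worth making because the profile probabilities could be read as clinical guidance, but it concerns an exploratory analysis only.

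**What to change.** Revise the predictor analysis as follows.

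1. Repeat the whole model-building step, including selection, in about 500 bootstrap samples.
2. Report apparent and optimism-corrected rho side by side, with a calibration slope.
3. Shrink the coefficients by that slope before computing any profile.
4. Show profiles with confidence intervals for outcomes named in advance, whether or not the model is significant. Label them exploratory and not validated.

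Do not add a rule that hides profiles when corrected rho is about zero. At n = 30 the correction leaves about 0.13 to 0.21 in noise models, so such a rule would still let many of them through. For the same reason, a slope of about 0.55 to 0.65 shrinks noise coefficients only in part, and the report should state that some optimism remains.

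The cost is a few hours of programming and no new data. The drawback is a less favourable reported fit, with residual optimism that has to be acknowledged.

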
#### Treatment As Usual

The ACG will receive TAU, which, according to IRP, comprises: a) paper and pencil cognitive activities to be performed at home 5 days a week, covering the same domains as the Ability Program (See Table 1), with five levels of difficulty progressively increasing week by week independently from participant’s performance the week before; b) prescription to perform light aerobic motor activity 7 days a week (e.g. walking for 30 min.); c) prescription to measure specific vital parameters according to individual clinical condition.

Before starting the program, the participant and carer dyad are invited at the Memory Clinic to collect the workbook containing paper and pencil cognitive activities and written clinicians’ prescriptions about motor activities and measurement of vital parameters. Researchers will provide the dyad with a brief training including instructions a) on the number of days per week in which to perform the exercises, at the same time encouraging the respect for pause periods; b) on the need to respect the dose of daily rehabilitation activities; c) on how to manage down-motivating drawbacks (especially in case of loss of perceived balance between skills and challenge in cognitive activities).

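### The profile figure called probability of treatment success is a patient's predicted chance of clinical improvement; treatment arm is not guaranteed in the model, so it does not by itself show success of Ability over TAU

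*Protocol article*

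**What the plan says.** All of the relevant text is in the Statistical analyses section of the protocol article.

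- **Outcome classes.** The plan states that "each outcome will be categorized in three intervals according to the criterion of a clinical improvement/stability/impairment which was set by expert physicians". The classes describe how the individual patient changed. They are not defined by comparison with the other arm.
- **Selection.** Factors that may predict change enter by forward stepwise selection at alpha 0.10, and the study is called exploratory at this point. The model is checked for proportional odds, so it is in effect an ordinal logistic model. The text neither forces arm in nor leaves it out, and it gives no candidate list.
- **Reported quantity.** "For each significant model, several representative profiles and their associated probability of a successful treatment will be computed".

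The same section assigns the Ability versus TAU comparison to a separate two-way ANOVA with a training-by-treatment interaction.

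The control arm is active. In the Treatment As Usual section the plan says: "The ACG will receive TAU, which, according to IRP, comprises: a) paper and pencil cognitive activities to be performed at home 5 days a week", together with prescribed motor activity and measurement of vital parameters.

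**The concern.** A predicted probability of being in the improvement class says how likely a patient with given characteristics is to improve. It becomes a statement about treatment only when it is set against the probability for the same patient under the other programme. The plan, followed as written, does not ensure that contrast. Stepwise selection can drop arm even if arm is a candidate, and success can occur under TAU as well as under Ability.

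The trial's aim is to compare Ability with TAU, and the Discussion stresses tailoring to the individual. Readers would naturally take profiles with a high probability of treatment success as showing who should be offered Ability. The same profiles could come from a model with no treatment term. They could also differ widely by baseline score when neither programme has any effect.

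**Working it through.** **The plan's own figure.** The Sample size section says that "a sample size of 30 subjects resulted in a power greater than 70" per cent, "considering α level of .05". It gives no effect size, SD or sidedness, so the figure can be neither confirmed nor refuted. With 1:1 allocation there are 15 per arm. The two-sided normal formula gives the standardised difference needed for 70% power:

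d = (1.960 + 0.524) × √(2/15) = 2.484 × 0.365 = 0.91

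A t-based calculation needs slightly more: d = 0.95 gives power 0.709. The value 0.91 serves below as a large effect, and 0.3 and 0.5 as smaller ones.

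**Check 1: can a selected model lack arm?** From the article: n = 30, 15 per arm, three ordered classes, forward entry at p < 0.10. Assumed: baseline-to-follow-up correlation 0.7, improvement or impairment as a change beyond ±0.5 SD, five candidates (arm, baseline score, three noise factors), and at most three terms entered. Proportional-odds models were simulated with 200 runs at d = 0 and 120 runs at each other effect. A model counts as selected when at least one factor enters.

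| True effect d | Any model selected | Arm in model | Model selected without arm |
|---|---|---|---|
| 0 | 0.75 | 0.125 | 0.625 |
| 0.3 | 0.875 | 0.35 | 0.525 |
| 0.5 | 0.875 | 0.54 | 0.33 |
| 0.91 | 0.96 | 0.86 | 0.10 |

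The last column is a share of all runs. Profiles exist only where a model is selected, and among those runs the share without arm is 0.33/0.875 = 0.38 at d = 0.5 and 0.10/0.96 = 0.10 at d = 0.91. With 120 runs the simulation standard error is √(0.33 × 0.67/120) = 0.043 at d = 0.5 and √(0.10 × 0.90/120) = 0.027 at d = 0.91.

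As a rough cross-check without simulated selection, arm tested alone at p < 0.10 by a t-test with 15 per arm passes with probability 0.38 at d = 0.5 and 0.78 at d = 0.91.

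**Check 2: how far can profiles differ with no programme effect?** Let the baseline score b and the follow-up score each have SD 1 and correlation ρ, with higher scores better and no effect in either arm. Then change given b is normal with mean −(1−ρ)b and variance 1−ρ². For an improvement cut-off of 0.5 SD:

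P(improvement | b) = 1 − Φ([0.5 + (1−ρ)b] / √(1−ρ²))

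| ρ | b = −1 | b = +1 |
|---|---|---|
| 0.6 | 1 − Φ(0.10/0.800) = 0.45 | 1 − Φ(0.90/0.800) = 0.13 |
| 0.7 | 1 − Φ(0.20/0.714) = 0.39 | 1 − Φ(0.80/0.714) = 0.13 |
| 0.8 | 1 − Φ(0.30/0.600) = 0.31 | 1 − Φ(0.70/0.600) = 0.12 |

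Over a wider range (ρ 0.5 to 0.9, cut-off 0.2 to 0.5 SD) the value at b = −1 runs from 0.18 to 0.64.

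**Check 3: what the contrast adds.** Averaged over baseline, at ρ = 0.7 and the same cut-off, the change has SD √(2 × 0.3) = 0.775. P(improvement) under TAU is 1 − Φ(0.5/0.775) = 0.26. If Ability adds 0.5 SD, it is 1 − Φ(0/0.775) = 0.50 under Ability. Only the difference, 0.24, is attributable to Ability over TAU. Neither probability alone shows it.

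**The case against.** The strongest reply is that much of the worry rests on silence. The article gives no candidate list, and a condensed article may leave that list, the forced terms and the profile definitions to the full plan. Arm may be a candidate and may enter, and profiles could then differ by arm. TAU is itself a treatment, so success could mean improvement under whichever programme was assigned. The step is exploratory, and the ANOVA makes the arm comparison. A probability that varies with baseline score is also what a prediction model should give.

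Most of this stands, and it rules out several stronger readings that a reader might infer:

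- *The figure is nothing but prognosis and regression to the mean.* It can be, but it need not be, because the text does not exclude arm.
- *Any improvement counts as success.* It does not. The class is clinical improvement by a criterion set by physicians, which may be meant to exclude small retest changes. Check 2 shows only that ordinary regression to the mean can cross a threshold of moderate size.
- *The arms are pooled, interaction terms are ruled out, or the classes refer to T1.* The text states none of these.
- *Every run without arm gives a misleading profile.* Runs that select no model give no profile and must not be counted.

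What survives is the label. The article does fix the selection rule, the within-patient classes and the name of the output. Under any candidate list, that name overstates the quantity unless arm is held in the model and profiles are contrasted by arm. Calling the step exploratory excuses a liberal entry level, but not a name that invites a causal reading. If success means improvement under either programme, the name should say so.

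**Conclusion.** The concern holds in a limited form. As described, the profile figure is a predicted probability of clinical improvement. It may come from a model without arm, and it does not by itself show that Ability succeeded over TAU.

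Under the assumed inputs, a selected model without arm arises in about one third of runs at d = 0.5 and about one tenth at d = 0.91. With no programme effect, profiles can differ from 0.12–0.13 to 0.31–0.45 on baseline score alone. The correlation, cut-offs, effect sizes and number of candidates are all assumptions, since the article gives none. The baseline result matters for the profiles only if baseline score, or a factor related to it, is a candidate.

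The damage would be to the interpretation of an exploratory analysis. A reader might infer that the main Ability versus TAU comparison is compromised. It is not, because the ANOVA does not depend on this step. The point is worth correcting but is not critical.

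**What to change.** - Force arm and the baseline score into every such model, and apply stepwise selection only to the other factors.
- For each profile, report the predicted probability of clinical improvement under Ability and under TAU, and their difference with an interval.
- Rename the quantity *predicted probability of clinical improvement*.
- Make no claim about who benefits from Ability on the strength of main-effect predictors alone.

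The cost is a few lines of analysis text and reporting, with no change to data collection. The downside is that with 30 patients the intervals will be wide and many profiles will show no visible difference between arms.
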